#### Statistical methods – secondary outcomes

The eight secondary endpoints will be compared between the two study arms as follows:Degree of MD in the IMF: Peak measured area (cm^2^) of patchy MD and confluent MD will be compared where data is available. It is anticipated that a good proportion of patients will have no MD and hence a measured area of zero. Thus, we will divide the outcome into four categories, the first being zero and the other three will be equal sized groups based on their area score. We will then use the linear trend chi-square test to determine whether the groups differ in their distribution of scores.Peak (worst) modified NCI CTCAE scores for radiation dermatitis will be compared using the chi-square test for trend [36].Dose-volume statistics: values for heart, lung, and body will be compared using the Mann–Whitney U test.Dose-area statistics (*in-vivo* dosimetry): Measured skin dose-area statistics will be compared within both study arms. The measured skin dose-area data for patients developing MD in the location where the dose was measured will be compared with that of patients not developing MD in that location to determine if a dose-area metric predictive of MD can be found for either arm.PRO: The peak (worst) PRO breast symptom scores will be compared using a between-groups t-test, or if data do not conform to test assumptions, the non-parametric Mann–Whitney U test. The requirement for steroid cream and analgesics will be compared using the chi-square test, or Fisher’s exact test, if appropriate.Clinical workflow: Time for patient setup will be compared between study arms using a between groups t-test.Reproducibility of patient setup, as assessed by variation in surgical clip positions measured on imaging will be compared between study arms using the F-test.Therapist satisfaction: Therapist satisfaction with the setup procedure as measured by the questionnaires will be compared using a linear trend chi-squared test.

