## Methods/Design

### Objectives

The primary objective of this study is to determine whether CARA V3.0 can reduce the incidence of moist desquamation in the IMF for patients with large or pendulous breasts undergoing breast RT in the supine position.

The secondary objectives of the study are as follows:To assess whether the severity of MD in the IMF can be reduced using CARA V3.0.To assess whether overall breast skin reaction scores can be reduced using CARA V3.0.To assess if CARA V3.0 reduces the volume of ipsilateral lung receiving 20 Gy or more (V20Gy).To assess if CARA V3.0 can reduce or maintain the volume of heart receiving 25 Gy or more (V25Gy) for left breast patients.To assess if CARA V3.0 can reduce the volume of body receiving greater than 50% (V50%) and greater than 105% (V105%) of the prescribed dose.To determine a dose-area parameter that is predictive of MD.To compare workflow and breast position reproducibility between the two study arms.To compare the PROs for quality of life measures and comfort during treatment setup between the two study arms.To compare radiation therapist experience between the two study arms.

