#### Treatment planning dose-volume statistics

The following dose-volume measurements will be acquired:◦ V20 Gy ipsilateral lung◦ V25 Gy heart◦ V105% body◦ V50% body◦ Breast separation (cm)The measurements will be reported as relative volume (% of structure volume), absolute volume (cm^3^), relative dose (% of prescribed dose), and absolute dose (Gy).Breast separation (cm) will be measured from beam entry to beam exit at the posterior beam edge at mid-breast level.

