### Interventions

#### Radiation therapy

For both study arms, breast RT protocols currently in use at the treating centres will be used. Dose fractionation schedules include 26 Gy in 5 daily fractions, 42.5 Gy in 16 daily fractions, 40 Gy in 15 daily fractions, 45 Gy in 25 daily fractions, and 50 Gy in 25 or 28 daily fractions. The extended fractionation schedules are generally reserved for patients with a large separation (> 24 cm) or significant post-operative changes. Partial breast treatments are acceptable if the inferior breast skin is included in the treated volume.

The treatment delivery will generally consist of a tangent pair of photon fields with or without internal mammary, supraclavicular, and/or axillary nodal fields. Combinations of 6 MV, 10 MV, 15 MV or 18 MV photons are permitted as required to meet planning dose constraints. Volumetric modulated arc therapy (VMAT) is currently under consideration.

Additional boost radiation to the tumour bed may be prescribed at the discretion of the radiation oncologist. Boost may be delivered using MV photons or electrons before, during, or following breast RT.

In both arms, patients will be planned and treated in the supine position on an angled breast board. In addition, patients must be indexed to the breast board and the breast board must be indexed to the treatment couch. Deep inspiration breath hold (DIBH) for left breast patients may be used to reduce dose to the heart [34] in both study arms. Standard skin care instructions will be utilized.

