#### Treatment planning and dose constraints

Treatment planning will be performed for both study arms according to current standard of care using the Varian Eclipse AAA algorithm (V13.6) or equivalent, as assessed at credentialing or during the trial if system upgrades occur. Correction for lung inhomogeneity will be used.

PTV, OTV or Breast_Eval coverage by the 95% isodose surface is required. The dose homogeneity objective is V105% < 2% of the OTV. Beam energy may be adjusted as required to achieve PTV coverage and homogeneity criteria, however PTV coverage will take priority over dose homogeneity if the latter cannot be met. For treatments of 15, 16, 25, or 28 fractions, ipsilateral lung V20 Gy shall be ≤ 15% of the lung volume (≤ 35% if regional nodes are treated) and V25 Gy heart shall be ≤ 5% of the heart volume. For 26 Gy in 5 fraction treatments, ipsilateral lung V8 Gy shall be ≤ 15% of the ipsilateral lung volume, heart V1.5 Gy shall be ≤ 30% and heart V7 Gy shall be ≤ 5% of the heart volume. Sliding window or field-in-field (step and shoot) IMRT may be used as available at the treating center.

All treatment plans in this study will be approved by the treating oncologists and designated physicists at each site, including a quality assurance check on all contours. All constraint violations will be noted on the planning data form.

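### Lung V20Gy and heart V25Gy are compared in one unstratified rank test across schedules in which those thresholds mean different things, and the protocol itself assesses 5-fraction plans with other metrics

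*Protocol article*

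**What the plan says.** All places are in the protocol article.

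- **Radiation therapy:** "Dose fractionation schedules include 26 Gy in 5 daily fractions", and goes on to 42.5 Gy in 16 fractions and "40 Gy in 15 daily fractions, 45 Gy in 25 daily fractions, and 50 Gy in 25 or 28 daily fractions".
- **Objectives:** one secondary objective concerns ipsilateral lung V20Gy. Another reads "To assess if CARA V3.0 can reduce or maintain the volume of heart receiving 25 Gy or more (V25Gy) for left breast patients". Neither is limited by schedule.
- **Treatment planning dose-volume statistics:** under "The following dose-volume measurements will be acquired" the list has lung V20Gy, heart V25Gy, body V105% and V50%, and breast separation. Lung V8Gy and heart V7Gy and V1.5Gy are not listed.
- **Treatment planning and dose constraints:** the lung V20Gy and heart V25Gy limits apply to 15, 16, 25 or 28 fractions. The passage that opens "For 26 Gy in 5 fraction treatments" sets limits on lung V8Gy, heart V1.5Gy and heart V7Gy instead.
- **Statistical methods – secondary outcomes:** "values for heart, lung, and body will be compared using" the Mann–Whitney U test. No stratification, adjustment or restriction is stated.
- **Randomization procedure and tracking** makes dose fractionation a stratum, and **Statistical methods – primary outcome** makes it a covariate.

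**The concern.** A threshold in absolute Gy picks out a different relative isodose when the prescription changes from 26 Gy to 50 Gy. The planning section recognises this by giving 5-fraction plans their own metrics. The endpoint list and the test do not. Following the plan as written ranks lung and heart values from all schedules together, so differences between schedules add spread that has nothing to do with the device.

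Organ sparing is a prominent claim for the device. The pilot reported a reduction in lung V20Gy (p = 0.005), and the Background treats lower organ doses as the demonstrated benefit. The monitoring committee may also weigh secondary outcomes at the interim analysis. A blunted test, or a pooled median that mostly reflects the schedule mix, would serve neither purpose. Body V50% and V105% are defined relative to the prescription and are not affected.

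**Working it through.** **1. The plan's own figure.** The only computed design figure is the primary sample size. With 50% vs 30%, two-sided α = 0.05, 80% power and pooled variance: n = [1.96·√(2·0.4·0.6) + 0.842·√(0.5·0.5 + 0.3·0.7)]² / 0.2² = 93 per arm, as stated. Allowing for 10% loss, 93/0.9 rounds up to 104, so 110 covers it. The article gives no power figure for the dose-volume endpoints.

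**2. Threshold as a share of prescription** (threshold ÷ prescribed dose).

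| Prescription | 20 Gy (lung) | 25 Gy (heart) |
|---|---|---|
| 26 Gy | 20/26 = 76.9% | 25/26 = 96.2% |
| 40 Gy | 50.0% | 62.5% |
| 42.5 Gy | 47.1% | 58.8% |
| 45 Gy | 44.4% | 55.6% |
| 50 Gy | 40.0% | 50.0% |

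The protocol's own 5-fraction metrics lie much lower: 8/26 = 30.8% for lung V8Gy and 7/26 = 26.9% for heart V7Gy.

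**3. What the constraints imply.** The volume above a higher dose lies within the volume above a lower one. For a 5-fraction plan that meets its limits, lung V20Gy ≤ V8Gy ≤ 15% and heart V25Gy ≤ V7Gy ≤ 5%. For 15–28 fractions the limits are lung V20Gy ≤ 15% (35% with nodes) and heart V25Gy ≤ 5%. These are ceilings only. They do not show how small the 5-fraction values are.

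**4. Possible size, by simulation.** None of these inputs is in the article except the arm size, 110 × 0.9 = 99. Assumed: conventional lung V20Gy with mean 12% and SD 4, an arm difference of 1.6 points (1.6/4 = 0.4 SD), 5-fraction values equal to the conventional ones times a scale factor, and the same schedule mix in both arms. Power of the pooled Mann–Whitney test, by 5-fraction share:

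| Scale factor | 10% share | 25% share | 50% share |
|---|---|---|---|
| 0.8 | 77% | 76% | 75% |
| 0.7 | 76% | 73% | 68% |
| 0.5 | not run | 59% | 49% |
| 0.1 | not run | 36% | 14% |

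With no 5-fraction patients, power is about 78–79%. At a 75% share it is 57% (scale 0.5) or 36% (scale 0.1); the loss eases when most patients share one schedule. With 3,000 runs the simulation error is about 1 point: √(0.5·0.5/3000) = 0.009.

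A rank test stratified by schedule (van Elteren) has about 76–79% power at scales 0.5 and 0.1 and shares of 25–75%, with type I error about 5%. The pooled test's type I error over the same settings is about 0.03–1.2%, well below the nominal 5%.

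**The case against.** The strongest reply is that these are secondary endpoints with no power claim, that the 5-fraction share is unknown, and that a modest shrinkage of 5-fraction values costs almost nothing (78% to 75–77% at scale 0.8). That stands, and it limits the size of the point. It does not remove the mismatch between the endpoint list and the planning section. Nor is this detail left to an analysis plan: the article states both the metric and the test.

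A reader might infer more than the article supports:

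- **Bias or false positives.** Randomization is stratified by fractionation, so the schedule mix should be similar in the two arms. The pooled test errs on the conservative side.
- **Near-zero 5-fraction values.** No distribution is given. This is plausible for heart V25Gy at 96% of prescription. It is weak for the lung: the PTV reaches the chest wall–lung interface and 95% isodose coverage is required, so adjacent lung can exceed 77%. Power figures built on exact zeros show the unfavourable end only.
- **Right-sided patients diluting the heart test.** The objective is already limited to left-breast patients. The one-line method omits this but does not say otherwise.
- **A null result read as "maintained".** The article nowhere says that non-significance will be read so. A margin or interval may be set in the analysis plan, which is not shown.
- **Stratifying by nodal treatment.** A different nodal limit for V20Gy does not make V20Gy invalid, and nodal treatment is not a randomization stratum. This is a preference.

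The article also plans to report relative as well as absolute dose. That helps description, but the named endpoints remain absolute thresholds.

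**Conclusion.** The point holds as a fault in a stated method. The threshold ratios are exact, and the endpoint and analysis sections disagree with the planning section about which metrics suit 5-fraction plans. The consequence is a conservative pooled test, a possible loss of power and a summary that mixes different isodoses. There is no bias between arms.

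The size is conditional. Under the assumed lung model, power moves from about 78% to 75–77% if 5-fraction values are slightly smaller, and to 49–59% if they are halved at a 25–50% share. It falls further if they are near zero, which is plausible mainly for the heart. If few 5-fraction patients enrol, the loss is small. The change is worth making because it is nearly free and fractionation is already used in randomization and in the primary model.

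**What to change.** 1. Reconcile Objectives, Treatment planning dose-volume statistics and Statistical methods – secondary outcomes with Treatment planning and dose constraints. State which lung and heart metric is the endpoint for 5-fraction patients and which for 15–28 fractions. The investigators should choose among the metrics and say why, including the role of heart V1.5Gy.
2. Replace the pooled Mann–Whitney test for lung and heart with a rank test stratified by fractionation group (van Elteren), and report medians and spread within each group. Both parts are needed: stratifying removes the spread between schedules, but it cannot recover information if a threshold leaves most 5-fraction values at or near zero.
3. State in the analysis section that the heart comparison is in left-breast patients, as the objective says.

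**Cost:** a wording change, plus extraction of the 5-fraction metrics from treatment plans that are retained in any case, since they are not on the list of measurements. No extra patients or procedures are needed. The change should be made before outcome data are compared by arm.

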### Patient population

This study is designed for patients having large or pendulous breasts resulting in IMF and/or lateral breast ptosis. The oncologist or radiation therapist will use an eligibility checklist to pre-screen for potential participants. Patients receiving nodal RT are eligible assuming the inclusion criteria are met. Enrolment in other studies at the same time is permitted at the discretion of the treating radiation oncologist. Waivers to eligibility criteria are not permitted.

Patient participation will be required for seven weeks after the start of breast RT with PRO questionnaires to be completed weekly, starting the last week of treatment and through to the duration of this seven-week period. Follow-up assessments with staff may be done in the clinic or remotely (e.g. Tele-Health, Zoom, phone, e-mail).

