### Statistics and analysis

#### Sample size calculation and recruitment period

Based on evidence from previous studies [5–8], we expect a control arm rate of 50% for any degree of MD in the IMF. Due to a reduction in skin folds and reduction in V105% with reduced breast separation, we hypothesize a rate of 30% moist desquamation in the study arm (i.e., an absolute decrease in incidence of 20%). For this effect size with 80% power and two-tailed α = 0.05, the sample size is 93 patients in each arm. Because of the nature of the study and 10% observed loss to follow-up in our pilot study, we will enroll 110 patients in each arm.

We expect that a 3-year recruitment period will be sufficient for the trial. A similar multicentre study from our team [5] achieved a similar recruitment rate in the same patient population drawing from only two centres.

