#### Randomization procedure and tracking

The random allocation lists will be computer-generated by a statistician not associated with the study. Randomization will use permuted blocks of random size. Stratification is by dose fractionation, by presence of IMF skin fold, and by centre.

The allocations will be uploaded into a password-protected website on secure hospital servers. When an eligible and consenting patient is identified in advance of their CT simulation appointment, the study coordinator or study radiation therapist will enter a patient identification code, and the computer will issue the allocation and a patient study number. An automated audit trail will track the patient identifier and study number, the treatment allocation, and the date, time, and site of the transaction.

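### Lung V20Gy is compared by a pooled, unadjusted rank test that ignores nodal irradiation, a strong expected driver of that endpoint; stratifying by planned nodal RT is a cheap improvement

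*Protocol article*

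**What the plan says.** Five places in the protocol article bear on this point.

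- **Objectives.** Lung dose is a named secondary objective: "To assess if CARA V3.0 reduces the volume of ipsilateral lung receiving 20 Gy or more (V20Gy").
- **Patient population and Radiation therapy.** The trial mixes nodal and breast-only patients. "Patients receiving nodal RT are eligible assuming the inclusion criteria are met", and tangents are delivered "with or without internal mammary, supraclavicular, and/or axillary nodal fields". The expected nodal share is not given.
- **Treatment planning and dose constraints.** The limit set for every schedule except the 5-fraction one reads: "ipsilateral lung V20 Gy shall be ≤ 15% of the lung volume (≤ 35% if regional nodes are treated"). The 5-fraction schedule has a lung limit on V8 Gy instead.
- **Randomization procedure and tracking.** "Stratification is by dose fractionation, by presence of IMF skin fold, and by centre". Nodal RT is not a stratum.
- **Statistical methods – secondary outcomes.** For the dose-volume statistics, "values for heart, lung, and body will be compared using the Mann–Whitney U test". No stratum, covariate or nodal subgroup is named. Covariate adjustment is specified only for the primary outcome, and nodal RT is not among those covariates.

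**The concern.** The protocol sets a V20Gy ceiling more than twice as high when nodes are treated, so it evidently expects nodal plans to irradiate more lung. If so, many of the pairwise comparisons behind a pooled Mann–Whitney statistic set a nodal patient against a breast-only patient. Those comparisons are decided largely by the nodal fields and carry little information about the device.

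Two things are at stake for the lung objective. A real V20Gy reduction is more likely to be missed. And if one arm happens to receive more nodal patients, the observed difference mixes that imbalance with the device effect, and the planned analysis has no way to separate them. Body V50% is exposed in the same way, because the nodal fields add to the treated body volume. Heart V25Gy may be too, since internal mammary fields are allowed.

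**Working it through.** **The plan's own figure.** The only sample size stated is for the primary endpoint. The protocol says "we expect a control arm rate of 50% for any degree of MD in the IMF" and assumes 30% in the device arm, with 80% power and two-sided 5%:

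n = [1.96·√(2·0.4·0.6) + 0.8416·√(0.5·0.5 + 0.3·0.7)]² / 0.20² = (1.3579 + 0.5708)² / 0.04 ≈ 93 per arm.

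This reproduces the stated 93. Allowing for 10% loss gives 93/0.9 = 103.3, so 104, and 110 per arm covers it. No power is stated for lung V20Gy.

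**What the documents give for V20Gy.** The ceilings are 15% and 35%, a gap of 20 points and a ratio of 35/15 = 2.33. These are limits, not means. The nodal share, V20Gy means, SDs and device effect are not given, so everything below rests on assumed values.

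**Number of patients.** V20Gy comes from the treatment plan, and data collected before withdrawal are kept. Loss during questionnaire follow-up therefore does not remove it, and up to 110 per arm are available.

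**Chance of imbalance.** The SE of the between-arm difference in nodal share is √(2p(1−p)/110). The chance of a difference of 10 points or more is 2[1 − Φ(0.10/SE)].

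| Nodal share p | SE (points) | P(difference ≥ 10 points) |
|---|---|---|
| 10% | 4.05 | 1.3% |
| 20% | 5.39 | 6.4% |
| 30% | 6.18 | 10.6% |
| 40% | 6.61 | 13.0% |

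A 10-point imbalance moves the difference in mean V20Gy by 0.10 × gap: 1.0 point for a gap of 10, 1.5 for 15 and 2.0 for 20.

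**Power.** The plain Mann–Whitney test was set against the van Elteren statistic, Σ[W_k − E(W_k)]/(n_k+1) divided by √(ΣVar(W_k)/(n_k+1)²), summed over the two nodal strata. Simulation: 4000 trials per cell, 110 per arm, two-sided 5%. Assumed inputs: breast-only mean 10% (SD 4), nodal mean higher by the gap (SD 6), device effect −1.5 points.

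| Nodal share | Gap 10: plain / stratified | Gap 15: plain / stratified | Gap 20: plain / stratified |
|---|---|---|---|
| 10% | 63.6 / 73.5 | 59.8 / 73.3 | 59.3 / 74.3 |
| 20% | 55.0 / 71.9 | 46.2 / 70.5 | 43.9 / 70.6 |
| 30% | 45.0 / 67.9 | 35.3 / 67.9 | 31.5 / 66.5 |
| 40% | 38.4 / 63.4 | 27.8 / 65.8 | 23.1 / 64.2 |

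The gain runs from 9.9 points (10% share, gap 10) to 41.1 points (40% share, gap 20).

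A second set of assumptions brings the means closer together. It used 99 per arm, slightly fewer than will have plans.

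- Means 10% and 25% (SD 3.5 and 6; effect −1.5, or −2.25 if nodal): 69 vs 82, 54 vs 81, 43 vs 80 and 37 vs 79 at shares of 10, 20, 30 and 40%.
- Means 11% and 18% (SD 4 and 6; effect −1.7, or −2.55 if nodal): gains of 4 points at a 10% share, 9 at 20% and 12–15 at 30–40%.
- Means 12% and 16%: gains of about 1–5 points.

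**Type I error with no device effect.** Over all randomisations both tests hold their level: 4.4–5.7% across the 110-per-arm scenarios. Given an imbalance they differ:

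- Nodal shares fixed at 25% vs 35%: plain 11.8%, stratified 5.4% (99 per arm).
- Nodal shares fixed at 15% vs 25%: plain 14.8%, stratified 5.6% (99 per arm).
- Across assumed inputs, an imbalance of exactly 10 points gives roughly 9–20% for the plain test. This falls back towards 5% as the two groups' means converge.
- Among trials with an imbalance of 10 points or more, the plain test rejects in about 18–32% (110 per arm).

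**The case against.** The strongest reply is that the planned test is valid. Chance imbalance in an unstratified factor is already covered by the 5% level, and the 10-point imbalance arises in only about 1–13% of trials. This stands. A reader might infer that the pooled test has an inflated false-positive rate or is systematically biased. It does not and is not. The distortion is conditional on an imbalance having occurred.

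A reader might also infer that the planning limits prove nodal RT to be the dominant determinant of lung V20Gy. The documents do not support that. The limits are ceilings, they do not cover the 5-fraction schedule, and no means or SDs are given. "Strong expected driver" is as far as the text goes.

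It is also tempting to contrast the pilot's p = 0.005 for lung V20Gy, from patients planned both with and without the device, with the between-patient comparison here. The article names neither the test behind that p-value nor whether any pilot patient had nodal RT, so nothing is built on it.

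Stratifying randomisation by fractionation might partly balance nodal RT. But the Radiation therapy section generally reserves the extended schedules for large separation or post-operative changes, not nodes, and the secondary analysis does not use the strata.

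Finally, adjustment of secondary analyses is often left to an analysis plan. Here, though, the protocol names the test itself and says that deviations from the original statistical plans will be described and justified, so the choice is fixed and open to comment.

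**Conclusion.** The point holds as an efficiency and conditional-bias issue on a secondary endpoint, and is best labelled a cheap improvement. The pooled test keeps type I error near 5% but gives up power, and it lets a nodal imbalance pass into the apparent device effect.

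The size cannot be determined from the protocol. Under assumed nodal shares of 10–40% and assumed means, stratifying gains from about 1 point of power (group means close) to over 40 points (means far apart, high nodal share). Given a 10-point imbalance and no device effect, false rejection is roughly 9–20%. All of this depends on the assumed share, gap, SDs and device effect. The stratified test was at least as powerful in every scenario examined and held about 5% under the null, so the recommendation does not depend on which assumption is right. The primary analysis is unaffected.

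**What to change.** In Statistical methods – secondary outcomes, replace the pooled test for lung V20Gy and body V50% with a van Elteren (stratified Wilcoxon) test stratified by planned nodal RT (yes/no). For consistency, do the same for heart V25Gy where nodal fields may affect it. Report the between-arm difference with its 95% CI within each nodal group. State that all patients with a treatment plan are analysed, up to 110 per arm.

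Define the stratum by the nodal intent recorded at enrolment, before allocation. The baseline list covers the RT prescription but does not name nodal intent. Table 1 also places the baseline assessment before first treatment, whereas randomisation comes before CT simulation. One yes/no field at enrolment is therefore needed so that the factor cannot be influenced by the allocated arm.

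The cost is that field, a sentence or two of analysis wording and slightly less simple reporting. No extra patients are needed. The change should be made before outcome data are seen, because adopting it after noticing an imbalance would look data-driven.
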